## Abstract

**Background:**

This project proposes a pilot study to investigate the positive healing effects of cognitive training with simple arithmetic and reading aloud on elderly postsurgical patients. Elderly patients undergoing surgery have an increased risk of Postoperative Cognitive Decline (POCD), a condition in which learning, memory, and processing speed is greatly reduced after surgery. Since elderly patients are more likely to exhibit symptoms of POCD, the incidence is increasing as the population receiving surgery has aged. Little effort has been expended, however, to find treatments for POCD. Learning therapy, which consists of a combination of reading aloud and solving simple arithmetic problems, was developed in Japan as a treatment for Alzheimer’s Disease to improve cognitive functions. Because patients with Alzheimer’s Disease experience similar issues as those with POCD in learning, memory, and processing speed, a cognitive intervention based on the learning-therapy treatments used for Alzheimer’s Disease could show advantageous outcomes for those at risk of POCD.

**Methods/design:**

Cognitive function will be measured before and after surgery using three different tests (Mini-Mental Status Exam, Frontal Assessment Battery, and Cogstate computerized tests). Subjects will be randomly divided into two groups—one that receives a Simple Calculation and Reading Aloud intervention (SCRA) and a waitlisted control group that does not receive SCRA. To measure cognition before and after the intervention, the previously mentioned three tests will be used. The obtained data will be analyzed using statistical tests such as ANCOVA to indicate whether the cognitive intervention group has made improvements in their cognitive functions. In addition, questionnaires will also be administered to collect data on mental and emotional statuses.

**Discussion:**

This report will be the first pilot study to investigate the beneficial effects of SCRA on elderly surgical patients. Previous studies have shown sufficient evidence on the effectiveness of learning therapy in healthy elderly people and in those with Dementia. Therefore, this study will clarify whether SCRA can improve cognitive function in the more specialized group of elderly surgical patients.

**Trial registration:**

University Hospital Medical Information Network Clinical Trial Registry, UMIN000019832. Registered on 18 November 2015.

**Electronic supplementary material:**

The online version of this article (doi:10.1186/s13063-016-1476-0) contains supplementary material, which is available to authorized users.

## Background

Memory loss and lack of concentration are symptoms that often occur in patients who have undergone surgery. These symptoms are part of a condition called postoperative cognitive decline (POCD), which is not an official diagnosis. Changes in cognitive abilities have been reported in elderly patients since the 1950s, and anesthesia has often been thought to be a potential culprit [1]. In 1955, Bedford [1] published a retrospective review of 1193 elderly patients who had surgery under general anesthesia over a 5-year period. He concluded that the cognitive problems were related to anesthetic agents and hypotension and that “operations on elderly people should be confined to unequivocally necessary cases.”

While most patients exhibiting POCD naturally recover from the condition in the 6 months after surgery, nearly 2 % of POCD cases last until death [1]. Thus, POCD can be divided into three categories: acute, intermediate, and long-term. Acute POCD is often used to describe cognitive decline detectable in the 1 week after surgery, intermediate POCD refers to cognitive decline detectable in the 3 months after surgery, and long-term POCD is used to describe changes lasting 1–2 years following surgery. A decline in cognition leads to difficulty in performing basic everyday activities [2–4], which results in a loss of independence [5]. POCD is also strongly associated with premature departure from the labor market [6]. Furthermore, people with POCD are at higher risk of death in the first year after surgery [7]. Consequently, maintaining or improving cognitive function in older adults is drawing increasing attention [8–23].

An international multicenter study on POCD reported memory impairments in 26 % of patients 60 years and older, with deficits reported to last for months to years [24]. Most notable instances of POCD are observed after cardiac and thoracic surgery [25]. Age is nevertheless the biggest risk factor for POCD [5, 24]. In addition, even healthy elderly adults may experience a decline in several cognitive functions, including memory [26], attention [27], executive functions [28, 29], and processing speed [30]. POCD is especially a problem because over the past 20 years, the number of older people undergoing surgical procedures has increased faster than the population is aging [25, 31].

However, very few studies have been conducted on the different methods for enhancing cognitive functions in a postsurgery elderly population. Nevertheless, several cognitive training programs have been shown to improve cognitive functions, including memory [16, 32], processing speed [19, 33, 34], executive function [17, 35], and attention [36] in a healthy elderly population. One such cognitive training method, learning therapy, has several beneficial points, which make it more appealing over other methods: 1) it can be conducted in healthy elderly people and in those suffering from dementia, 2) it is cost-efficient because special machinery and devices are unnecessary, and 3) the burden on participants is minimal because learning therapy takes only 15–30 minutes each day.

Learning therapy consists of two simple and easy training tasks (reading Japanese aloud and solving easy arithmetic) derived from knowledge of neuroscience. Brain imaging studies indicate that reading sentences or words aloud [37–41] and simple arithmetic operations [42–44] activate the frontal cortex and of the temporal and parietal association cortices. Thus, learning therapy was specially designed to stimulate these cortices via the cognitive tasks, thereby promoting improvement in the function of these cortices [45, 46]. Previous studies using learning therapy have demonstrated that it can improve executive functions and processing speed in healthy elderly people. One such study by Uchida and Kawashima [35] conducted a randomized controlled trial using learning therapy for healthy elderly people. Participants were divided into a learning therapy group and a waitlisted control group. The learning therapy group was required to do two training tasks for 5 days a week: reading Japanese aloud and conducting simple calculations. After 6 months, the learning therapy group showed improved scores in the frontal assessment battery (FAB), which measures executive function [47–49], and a digit-symbol substitution test, which measures processing speed [50]. These results suggest that learning therapy beneficially affects some cognitive functions in elderly people.

However, learning therapy is conducted every day with a weekly visit to the learning facility. Since the participants in this pilot study will be undergoing surgery, such an intense course of training is not reasonable. As a result, this pilot study will incorporate a modified, less-intensive version of learning therapy, and henceforth will be referred to as the simple calculation and reading aloud (SCRA) intervention. To measure changes in cognitive function due to surgery, this study will incorporate several cognitive tests, in addition to the conventionally used MMSE-J. These tests will determine what cognitive functions decline, and to what degree. Furthermore, we will examine to what extent the cognitive intervention improves cognitive functions in the elderly population after surgery. Several health questionnaires will also be administered to determine mental and emotional wellbeing. In addition, the type of general anesthetic administered, the amount of anesthetic administered, the anesthesia duration, the surgery duration, age, and sex will be noted.

### Purpose

This study is an open-label randomized control trial utilizing a between-group design to examine 1) to what extent cognitive function is reduced after surgery and 2) whether cognitive training focusing on SCRA will improve cognitive functions in elderly patients after surgery. The first and second aims of this study are independent of each other. A decline in SCRA function after surgery is expected, especially in the elderly population from which the participants will be chosen. Previous results conducted in a healthy elderly population suggest that cognitive intervention should improve cognitive functions. If the cognitive intervention is successful for treating patients with higher risk of POCD, this noninvasive method could greatly improve their quality of life.

As mentioned above, no standardized method exists to diagnose a patient with POCD. In addition, due to the limited number of participants, we lack the data necessary to mirror previously employed methods [5, 24, 25] that determine whether each individual patient has POCD. Therefore, this study will investigate 1) the effect surgery has on the cognitive functions of the group of participants undergoing surgery and 2) the effects of SCRA intervention on the same participants, all of whom will fall under the population category of “elderly” and “post-surgical.”

## Methods/design

The trial protocol was developed according to the SPIRIT and CONSORT guidelines for randomized controlled trials [51]. Please see Additional file 1 (CONSORT guidelines) and Additional file 2 (SPIRIT).

### Randomized controlled trial design and setting

This study is an open-label, randomized, controlled trial conducted in Sendai City, Miyagi Prefecture, Japan. Each participant in this study will provide written informed consent prior to participating. The protocol of the study and the consent form have been approved by the Ethics Committee of the Tohoku University Graduate School of Medicine. This study was registered with the University Hospital Medical Information Network (UMIN) Clinical Trial Registry (UMIN000019832).

To assess the effects of SCRA on elderly patients who have undergone surgery, all the participants will be randomly assigned to one of two groups: the SCRA intervention group and the waitlisted control group, which does not undergo the SCRA intervention. The study design is shown in Figs. 1 and 2.

**Fig. 1 Fig1:**
[figure not shown]
CONSORT flowchart

**Fig. 2 Fig2:**
[figure not shown]
The timeline of the study indicates when the questionnaire and cognitive function tests will be administered. The tests will be administered to the participant on three occasions. The first time will be before the surgery as a baseline. The tests will be administered a second time after surgery to determine whether the surgery affected cognitive functions. The participants will be randomly split into two groups: 1) the group that receives SCRA cognitive intervention and 2) the waitlist control group. The cognitive intervention group will continue the cognitive intervention for 12 weeks. The no-SCRA control group will continue life as normal for 12 weeks. After 12 weeks, both groups will be administered the final round of tests to determine if SCRA intervention improved cognitive functions. The tests will be conducted in a ward or outpatient room at Tohoku University Hospital of Thoracic Surgery

### Recruitment of participants

Respiratory patients undergoing lung surgery will be recruited from Tohoku University Hospital. Patients admitted to the hospital prior to surgery will be informed about the study. If interested in participating, the patient will receive both a written and a verbal explanation of the study and be asked to sign the approved informed consent form.

### Eligibility criteria

Approximately 50 volunteers will be recruited from respiratory patients undergoing lung surgery with general anesthesia lasting 2–8 hours. As previously mentioned, this is a pilot study, so 25 volunteers in each group should be enough to provide information on the changes in cognitive function. Participants must be native Japanese speakers who are 60 years and older and self-report to be right-handed. Participants should be unconcerned with their memory functions. A thoracic surgery physician from the Tohoku University Hospital will refer potential participants. Other data that will be recorded includes the type of general anesthesia, the amount of anesthesia administered, duration of anesthetic administration, duration of surgery, age, and sex. These additional data will be collected by the collaborating surgeons.

### Randomization and blinding

Participants will be randomly placed into one of two groups: 1) the group undergoing SCRA cognitive intervention and 2) the no-SCRA waitlisted control group. Random assignment using an online computer program (http://www.graphpad.com/quickcalcs/index.cfm) will take place after informed consent and baseline testing. Participants are stratified by gender and randomized to SCRA or waitlisted control groups. In order to obtain a similar size for both groups, blocked randomization (block size 4) is applied with an allocation ratio of 1:1. Since the participants of the study are patients undergoing cognitive intervention or are being waitlisted, designing a blinded study is difficult. As a result, the trial design is open-label.

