### Waitlisted control group

The waitlisted control group will also be randomly selected from the pool of participants after surgery. During the duration of the study, the waitlisted control group will continue life as usual and will not receive SCRA cognitive intervention. After completing the study, they will be given the opportunity to experience the cognitive intervention. No placebo will be used for this group. Results from previous intervention studies [32, 64] report that a placebo group is unnecessary for this type of study because no differences were observed in cognitive function improvement between the placebo group and the control groups. These participants will also travel to the hospital to meet with their doctors. As with the experimental group, during these visits, control group participants will also be queried about their daily habits. Twelve weeks after surgery the control group will be administered the final round of tests (MMSE-J, FAB, CBB, and health questionnaires).

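### One fixed block size of 4, stratified by gender only, in an open-label single-hospital trial makes up to about 31–32% of assignments deducible at the moment of randomisation

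*Protocol article*

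**What the plan says.** Under Randomization and blinding, the article states that "blocked randomization (block size 4) is applied with an allocation ratio of 1:1", and that "Participants are stratified by gender and randomized to SCRA or waitlisted control groups". The reason given for blocking is similar group sizes. The same section explains why blinding is difficult and concludes: "As a result, the trial design is open-label".

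Patients come from a single hospital (Recruitment of participants: "Respiratory patients undergoing lung surgery will be recruited from Tohoku University Hospital"), and candidates are put forward by one of its own doctors (Eligibility criteria: "A thoracic surgery physician from the Tohoku University Hospital will refer potential participants"). The target is about 50 patients.

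The timing of randomisation is described in two ways. Randomization and blinding says that it "will take place after informed consent and baseline testing". Waitlisted control group says: "The waitlisted control group will also be randomly selected from the pool of participants after surgery".

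**The concern.** With a fixed block of four at 1:1, every block holds two assignments to each arm. In an open-label trial the past assignments are visible. With one hospital and two easily recognised strata, two short tallies show where each current block stands. Once one arm has used its two places, the rest of the block is known.

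Hiding the allocation list does not prevent this, because the deduction uses past assignments and not the list.

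There is some room to act on such knowledge. Candidates are referred by a physician, one entry criterion concerns the patient's own view of their memory, and pending patients could be assigned in a chosen order. The analysis adjusts for pre-training score, sex and age (Statistical analysis). It does not adjust for motivation or expected recovery, on which selection could act. With about 25 patients per group, a few steered assignments could matter.

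**Working it through.** The article gives no predictability figure, so there is none to reproduce.

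**Inputs.** Block size 4, ratio 1:1, two gender strata and open-label conduct (Randomization and blinding); about 50 patients (Eligibility criteria); recruitment January to August 2016 (Trial status).

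**1. Assignments known with certainty in a complete block.** There are six equally likely sequences: AABB, ABAB, ABBA, BBAA, BABA, BAAB. Positions 1 and 2 are never determined. Position 3 is determined when the first two match (AABB, BBAA): 2/6 = 1/3. Position 4 is always determined.

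Known per block = 0 + 0 + 1/3 + 1 = 4/3. Share = (4/3)/4 = 33.3%.

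**2. Best guess in a complete block.** The chance of being right is 1/2 at position 1, 2/3 at position 2, 1/3 + (2/3)(1/2) = 2/3 at position 3, and 1 at position 4. The sum is 17/6, so the rate is 17/24 = 70.8%, against 50% by chance.

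**3. Fifty patients in two strata.** The last block in a stratum is usually incomplete, which lowers the total.

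| Gender split | Known in first stratum | Known in second stratum | Total of 50 |
|---|---|---|---|
| 25 / 25 | 6 × 4/3 = 8.00 | 6 × 4/3 = 8.00 | 16.0 (32.0%) |
| 20 / 30 | 5 × 4/3 = 6.67 | 7 × 4/3 = 9.33 | 16.0 (32.0%) |
| 15 / 35 | 3 × 4/3 + 1/3 = 4.33 | 8 × 4/3 + 1/3 = 11.00 | 15.3 (30.7%) |

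Over all possible splits the range is 15.3 to 16.0. At 25/25 the best guess is right for 2 × (6 × 17/6 + 1/2) = 35 of 50, or 70.0%.

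**4. Prediction made before randomisation.** Suppose one earlier same-sex patient is still unassigned when the prediction is made. Then only position 4 can be known, and only if the first two assignments match: (1/3)/4 = 1/12 = 8.3%. With two pending, nothing is certain.

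As an illustration, assume 50 patients arriving evenly over about 35 weeks, equal numbers of each sex and Poisson arrivals. That is 50/35/2 = 0.714 same-sex patients per week.

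- One-week gap from referral to randomisation: P(0 pending) = e^−0.714 = 0.490 and P(1) = 0.350. Known = 0.490 × 1/3 + 0.350 × 1/12 = 19%.
- Two-week gap: P(0) = 0.240 and P(1) = 0.342. Known = 0.240 × 1/3 + 0.342 × 1/12 = 11%.

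**5. Effect of varying the block size.** This was simulated with 25 patients per stratum, sizes 4 and 6 equally likely, and an observer who knows the possible sizes but not their order.

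| Scheme | Known with certainty | Best guess right |
|---|---|---|
| Fixed 4 (simulated, same setting) | 32.1% | 70.0% |
| Random 4 and 6 | 5.7% | 68.3% |

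A fixed block of 6 would leave 25% known (complete blocks).

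**The case against.** The strongest objection is about timing. Patients are informed and recruited on admission before surgery and randomised later, so a referring physician must predict an assignment that lies ahead, with other patients possibly pending. Step 4 shows that the certain share at referral can be far below one third. This stands. A reader might infer that staff know a third of assignments when deciding whom to approach, but the documents do not support that. The two timing statements do not fix one time point. A post-surgery draw is also after baseline testing, so the first statement does not exclude the second, but a draw immediately after baseline would leave fewer patients pending. A delay also leaves staff free to choose the order in which pending patients are assigned.

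Knowledge of the block size is also assumed. The documents do not say who runs the online randomisation tool, whether the referring physician knew the block size, or whether the article appeared before recruitment ended. This stands too, so the point is what informed staff could deduce.

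Other entry criteria (age, native language, self-reported handedness, length of anaesthesia) leave less room for manipulation. The article calls the study a pilot, expects non-significant effects, and concedes possible motivational bias from the untreated control group. These points limit the weight of the finding but do not remove it.

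Finally, who generates, holds and releases the list is detail that an article may leave to the full protocol, so its absence is not criticised here. The stated fixed block size is what creates the predictability.

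**Conclusion.** The point holds as an avoidable risk of selection bias. With the stated scheme, 15 to 16 of 50 assignments (30.7% to 32.0%) could be deduced with certainty at the moment of randomisation. This assumes that staff know the block size, track assignments by gender and have no earlier same-sex patient pending. The share is 8.3% with one pending and zero with two.

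Two stronger readings should be resisted. Applying one third to all 50 gives about 17 (50/3 = 16.7), which ignores incomplete last blocks. And nothing in the article shows that referral or order of assignment was actually influenced, so bias is not demonstrated. The weakness should be corrected, but it does not invalidate a pilot.

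**What to change.** In Randomization and blinding, replace the single block size of 4 with block sizes that vary at random, for example 4 and 6, within each gender stratum. Do not disclose the sizes or their order to referring, recruiting or testing staff. Recruitment began in January 2016, so complete the open blocks, apply the new scheme to the remaining participants, and acknowledge the risk for those already assigned. State one time point for randomisation in both sections that mention it.

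The cost is a new list for the remaining participants and a documented change during the trial. The possible difference between groups within a stratum rises from 2 to 3 (over both strata, at most 6 instead of 4). The gain lies almost wholly in removing certainty, since the best-guess rate hardly moves. For patients assigned before the change and in the open blocks, the predictability remains.

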### Determining postsurgical cognitive function

First, the Mini-Mental State Examination-Japanese (MMSE-J) will be administered to the participant after receiving consent. The MMSE-J is a 30-point questionnaire used extensively in both clinical and research settings to measure cognitive impairment [52]. To assess dementia, clinicians will consider a person’s MMSE-J score along with their history, a physical health exam, symptoms, and results from other tests. A higher MMSE-J score indicates better cognitive performance. The MMSE is the most common mental status test used to determine POCD [53, 54]. For test-retest intervals of 2 months or less, the MMSE has been shown to have good test-retest reliability [53, 55, 56].

Following the MMSE-J, the participant will be given the Frontal Assessment Battery (FAB). The FAB is an 18-point questionnaire that is commonly performed at bedside or in a clinical setting to help measure cognitive impairment in executive functions [47–49]. Again, higher scores indicate better performance. The Japanese translation of the FAB has previously been shown to be comparable to the original English versions and has a good test-retest reliability at 3 weeks [48, 49]. Both the MMSE and FAB are commonly administered in studies determining cognitive decline [57–59].

After the FAB, the participant will be given a laptop running the Cogstate software to measure the speed of processing, visual attention, and visual learning and memory via Cogstate’s “Brief Battery” (https://cogstate.com/). This computerized battery has been shown to effectively determine cognitive decline [25, 60]. Previous studies on the test-retest reliability of the CBB have indicated that there are no retest-related increases in scores after 1 month. However, the retest scores have been shown to increase at 1 week or less [60–62]. Additionally, the Japanese version of the CBB has previously been shown to yield reliable results for Japanese subjects [63]. This computerized test will be administered via a laptop. Trained project investigators will give detailed instructions and will be nearby to provide reassurance to the elderly participants and to help with any confusion regarding computer use. In order to measure these indicators, the software will run four tasks in sequence, which lasts approximately 15 min in total. First, the software will run a detection task to measure the speed of processing. The participant will be asked to hit the “Yes” button when the trump card turns face up. The unit of measurement will be Log10 milliseconds of the reaction times for correct responses. Incidentally, a lower score indicates better performance. The next task will be an identification task to measure visual attention. The participant will be asked to press “Yes” if the card is red and “No” if the card is black. Again, the unit of measurement is Log10 milliseconds of the reaction times for correct responses. The third task is a one-card memory task in which the participant is asked to press “Yes” if they have already been shown the card. The accuracy of performance will be measured with the arcsine transformation of the square root of correct responses. Therefore, a higher score indicates better performance. The final task is a working memory task called “One Back,” in which the participant is asked to press “Yes” if the card is the same as the previous card, and “No” if it is different. The accuracy of performance is measured using the arcsine transformation of the square root of the proportion of correct answers. Again, a higher score reflects better performance.

These tests will be administered and scored by trained project investigators, and they will be administered to the participant three times: 1) prior to surgery as a baseline, 2) after the surgery to determine a decline in cognition (about 1 week after surgery), and 3) 12 weeks after surgery to determine the effects of SCRA. The type of general anesthesia administered, the amount of anesthesia administered, the anesthesia duration, the surgery duration, age, and sex will be noted. Additionally, several health questionnaires will be administered to determine emotional and mental wellbeing.

